#### Primary outcome variable

The primary outcome measure is students’ post -intervention participation in out-of-school physical activity at the pre-trial, post-trial, one-, three and 6 month follow-up data collection occasions. Physical activity participation will be measured using the short form of the International Physical Activity Questionnaire, IPAQ [42], which will be modified to make explicit reference to out-of-school physical activity. The IPAQ comprises four items recording the frequency (number of days) and duration (hours) of participation in moderate and vigorous physical activity, walking, and sitting over the past 7 days. The physical activity score for moderate and vigorous physical activity and walking is calculated based on norms and expressed in MET-minutes per week. A score for total physical activity in out-of-school contexts is provided by the sum of the duration and frequency of vigorous, moderate and light physical activity scores. The IPAQ has acceptable concurrent validity and reliability indices [43].

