### Sample size

A statistical power analysis was conducted to estimate the required sample size for student data based on a path analysis according to published recommendations [56]. The analysis was based on a model in which the primary outcome variable of student’s participation at each post-intervention follow-up occasion was regressed on the intervention condition (dummy coded as 1 = received intervention, 0 = received control) and constructs from the trans-contextual model (perceived autonomy support, autonomous motivation in PE and out-of-school, attitudes, subjective norms, perceived behavioural control, and intentions) as simultaneous predictors. Statistical power (beta) was set at 0.90 and statistical significance level (alpha) was set at 0.05, and confidence intervals of 0.068 and 0.080 for the root mean square error of approximation fit index based on previous trans-contextual models [9]. The analysis indicated that a student sample size of 286 is required to detect the effect size based on model fit. Based on typical attrition rates of 40% reported in the literature in multiple follow-up studies of physical activity [57, 58] we aim to recruit 476 student participants at baseline (*n* = 238 participants per intervention group).

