### Data analysis

Multilevel structural equation modelling using the Mplus, v. 8.0 software [59] will be used to test our hypotheses. All analyses will be performed using intention-to-treat analysis and supplemented by per-protocol analyses for all planned outcome variables [60]. Where data is missing for the psychological variables, we will impute missing values using linear interpolation if the data is confirmed missing completely at random. We expect to have data on our primary and secondary outcome measures, as well as mediating measures, at pre-trial and at the allotted follow-up occasions after the delivery of the intervention (post-trial, and at the one-, three-, and six-month follow up data collection occasions after the implementation period). We also expect to have self-report data on parenting from students and their parents or guardians at pre-trial. Student data will be nested within school and teacher/class, and therefore variance in outcome variables may be attributable to school-level and class-level variation as well as variation between students attributable to the intervention itself. Effects of the intervention on study outcomes can be interpreted at the student level after controlling for school- and class-level effects. Our longitudinal design enables also the examination of potential trajectories in the development of outcome variables. We will test the model at each of the follow-up time points with students’ out-of-school physical activity as the primary dependent variable, the intervention condition as a dummy-coded independent variable (1 = intervention group; 0 = control group), and the psychological variables (perceived autonomy support from teachers, autonomous motivation in PE and out-of-school physical activity, attitudes, subjective norms, perceived behavioural control, intentions), as simultaneous predictors. We will statistically control for each of model variables from the previous time point using the standardized residual scores.

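### Adjusting through standardised residual scores takes the primary outcome off the MET-minute scale, makes effects non-comparable across occasions, and can attenuate mediator paths

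*Protocol article*

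**What the plan says.** Under Primary outcome variable, the physical activity score "is calculated based on norms and expressed in MET-minutes per week", and it is collected "at the pre-trial, post-trial, one-, three and 6 month follow-up data collection occasions". Under Data analysis: "We will test the model at each of the follow-up time points with students’ out-of-school physical activity as the primary dependent variable". The predictors are "the intervention condition as a dummy-coded independent variable (1 = intervention group; 0 = control group") and seven psychological variables entered simultaneously. The section then states: "We will statistically control for each of model variables from the previous time point using the standardized residual scores".

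The article mentions no back-conversion to MET-minutes and no fixed reference SD. Its one imputation rule covers the psychological variables. The same section promises to examine trajectories. The Discussion lists long-term effectiveness, and how the intervention works through the model constructs, among the study's contributions.

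**The concern.** A residual score that controls for the previous occasion is the current value regressed on the previous one. Standardising divides it by its own SD. Three things follow.

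- **Unit.** The condition coefficient is in residual-SD units, and that unit depends on how stable activity is between the two occasions. The gaps differ: about six weeks from pre-trial to post-trial (two weeks of training plus one month of implementation), then about one, two and three months. The stability, and so the unit, will probably differ too.
- **Reference.** From the one-month follow-up on, the previous occasion lies after randomisation, so residualising removes part of any effect that has been maintained.
- **Mediation.** Residualising each variable only on its own past is not the same as adjusting jointly for all earlier values.

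At stake are the comparison of effects over follow-up, the reading of an effect as an amount of activity, and the mediator paths.

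**Working it through.** **Inputs.** The document gives neither the SD of MET-minutes nor the correlation r between successive occasions. I assume r = 0.5 to 0.8 and a true effect of 0.20 raw SD, with equal SDs across occasions. The Sample size section supplies no alternative: it rests on "confidence intervals of 0.068 and 0.080 for the root mean square error of approximation fit index" and concludes that "a student sample size of 286 is required to detect the effect size based on model fit", with no intervention effect in MET-minutes or SD units. Its attrition step reproduces within rounding (286/0.60 = 476.7; stated 476 = 2 × 238), but this point does not depend on it.

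**Step 1, pre-trial to post-trial.** The previous score carries no intervention effect, and the residual SD is SD × √(1 − r²). The reported coefficient is 0.20/√(1 − r²).

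**Step 2, later occasions.** If the difference is maintained, the previous score already contains it. The raw residual difference is about 0.20(1 − r), and the reported coefficient is about 0.20(1 − r)/√(1 − r²).

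| r | Post-trial, residual score | Later, residual score | Later, raw scale, previous occasion as covariate | Any occasion, raw scale, pre-trial as covariate |
|---|---|---|---|---|
| 0.5 | 0.23 | 0.115 | 0.10 | 0.20 |
| 0.6 | 0.25 | 0.100 | 0.08 | 0.20 |
| 0.7 | 0.28 | 0.084 | 0.06 | 0.20 |
| 0.8 | 0.33 | 0.067 | 0.04 | 0.20 |

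Large-sample simulation agrees: 0.114, 0.101, 0.080 and 0.065 for the later residual scores, and 0.100, 0.082, 0.058 and 0.039 for the raw scale with the previous occasion as covariate. At r = 0.6 throughout, an unchanged MET-minute difference would be reported as 0.25 at post-trial and 0.10 afterwards, an apparent fall of 60% (1 − 0.10/0.25).

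For six months the table is illustrative only. The Procedure section has the wait-list group trained straight after the three-month follow-up, so a maintained group difference need not be expected there.

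**Step 3, mediator path.** Simulated model: true path from mediator to activity at the same occasion 0.20; pre-trial correlation of mediator and activity 0.4; stability 0.5 or 0.6.

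| Assumed cross-lags | Path from residual scores, rescaled to raw units | Path with joint covariates |
|---|---|---|
| None | 0.20 | 0.20 |
| Earlier mediator to later activity only, 0.2 | 0.20 | 0.20 |
| Earlier activity to later mediator, 0.1 | 0.19 | 0.20 |
| Earlier activity to later mediator, 0.2 | 0.17 to 0.18 | 0.20 |
| Both directions, 0.2 | 0.15 to 0.16 | 0.20 |

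**Step 4, missing values.** A residual needs both occasions. A student absent at one occasion and present at the next has an observed outcome at the second that cannot enter the analysis.

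**The case against.** - **The wording is one loose sentence.** It does not spell out that variables are replaced by saved residuals. That is so. Replacement is an inference, but the natural one, and the article names the method, so this is a stated choice and not detail left to a fuller plan.
- **Rescaling is not an inferential error.** Dividing by a constant leaves the test at an occasion unchanged, and multiplying by the residual SD restores raw units. This stands. Nothing forbids back-conversion, but none is mentioned, and it would not undo the removal of a maintained effect in Step 2. Once rescaled, the bias in the post-trial condition coefficient is small, roughly 5% and at most about 8% in the scenarios tried.
- **Moving to covariates is not enough.** This also stands. Keeping the previous occasion as covariate on the raw scale still gives 0.10 down to 0.04, a wider relative spread than the residual scores show at those occasions. The adjustment must be for the pre-trial value.
- **The condition coefficient is a direct effect on any scale**, because the psychological variables are in the model with it. True, and changing the score does not alter it.
- **Missing outcome data may be handled in the full analysis plan.** Possibly. The loss in Step 4 nevertheless arises from the scoring method itself.

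A reader might infer from the post-trial column that effects are inflated throughout follow-up, by up to 44% between r = 0.5 and r = 0.8 (1.67/1.15). The plan does not support that, because at later occasions the adjustment is for a post-randomisation score and the reported effect falls as r rises.

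**Conclusion.** The point holds and should be acted on. On the natural reading, the analysed primary outcome is not in its defined unit. A constant 0.20 SD effect would be reported as 0.23 to 0.33 at post-trial, and a maintained one as about 0.11 to 0.07 later, for assumed r of 0.5 to 0.8. The exact values rest on those assumptions; the dependence on r holds whenever r is not zero. This undermines the trajectory and long-term aims.

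The mediator attenuation is conditional. It appears only if earlier activity influences the later mediator, and its size (0.20 to between 0.15 and 0.19) depends on cross-lags that the document does not give.

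Three stronger readings are not supported:

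- that the scaling invalidates the test at a given occasion;
- that all mediator paths are necessarily biased;
- that a missed occasion costs two outcome values because of this method. The missed value is lost under any method, so the extra loss is one.

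**What to change.** - Drop the standardised residual scores.
- Keep out-of-school physical activity in MET-minutes per week as the dependent variable.
- For the intervention effect at each occasion, enter the pre-trial value, not the preceding post-randomisation value, as a covariate in the same multilevel model. Say whether the reported difference is the total effect or the effect with mediators held fixed.
- For mediator paths, enter the earlier values of all model variables jointly as covariates.
- Estimate by full-information maximum likelihood with the covariates included in the model, so that students with a missing earlier value are kept.
- Report the adjusted difference in MET-minutes per week. Base any standardised effect on one common pre-trial SD at every occasion.

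This changes analysis wording only. It needs no new data, and the Mplus multilevel models already planned can do it.

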### Objectives

The purpose of the current protocol article is to report the development of a school-based intervention based on the trans-contextual model to promote secondary school students’ physical activity participation by fostering autonomous motivation (the PETALS trial). The trial will adopt a cluster-randomized waitlist-control design, and participants will be teachers of lower-secondary school PE classes and their students. The intervention will involve initial training of PE teachers of lower-secondary PE classes on the use of autonomy support strategies in their regular lessons, followed by an implementation period in which teachers apply their training in regular PE classes. Effects of the intervention will be evaluated through changes in subsequent follow-up measures of participating students’ physical activity levels and trans-contextual model variables relative to pre-trial baseline measures. We will also evaluate effects of the intervention on PE teachers’ autonomy-supportive behavior measured using self-report and observation. We will also control for support for autonomy from parents and peers. Other salient demographic and individual difference variables will be also controlled for. We expect the research will provide formative evidence of an effective, replicable, low-cost behavioural intervention, which will help in developing long-term participation in physical activity in young people. In addition, key deliverables of the research will be a set of training materials and an intervention manual, which will provide step-by-step accessible instructions on how to implement the intervention and can be disseminated to schools with no specialist knowledge and minimal cost.

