## Discussion

School PE is an existing network with considerable potential for the delivery of interventions to promote physical activity to a captive audience of young people. Such interventions are also consistent with PE curricula to promote lifelong physical activity and health. However, relatively few studies have examined the effectiveness of school-based PE interventions in promoting out-of-school physical activity. The goal of the proposed study outlined in this protocol is to address this gap in the literature by testing the effectiveness of a theory-based intervention delivered in PE to promote lower secondary school students’ physical activity outside of school. The intervention will capitalize on the trans-contextual model [6, 10], a motivation model which specifies the processes by which teachers’ support for students’ self-determined or *autonomous* motivation in school translates to their autonomous motivation, beliefs, and intention toward, and actual participation in, physical activity outside of school.

The intervention will make a unique contribution to knowledge in four areas: (i) it will test the effectiveness of a theory-based in-school intervention delivered by PE teachers in promoting lower secondary school students’ physical activity participation outside of school, which has seldom been demonstrated; (ii) it will evaluate how the intervention works in promoting students’ out-of-school physical activity participation through effects of intervention on key constructs from the trans-contextual model; (iii) it will outline the development and implementation of a cost-effective, replicable theory-based teacher training program to train teachers to use autonomy-support techniques in their PE lessons and promote out-of-school physical activity; and (iv) it will evaluate the long-term effectiveness of the intervention in promoting physical activity behaviour through one, three, and six-month post-intervention follow-up of behavioural and theory-based outcomes.

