Although school PE has been identified as an important existing network in which messages and interventions promoting out-of-school physical activity participation could be promulgated, interventions to promote out-of-school physical activity through school PE are rare and these studies often only have limited follow-up periods of behavioural outcomes. For example, a previous study [63] demonstrated the effectiveness of a PE delivered intervention aimed at promoting physical activity participation in high school students. However, the study adopted a relatively brief intervention, relied exclusively on self-reported physical activity measures, and only adopted a relatively short term follow-up of students’ behaviour. Our proposed intervention will advance this research by developing a comprehensive autonomy support training program with an associated set of training materials, use accelerometry to verify self-report measures of physical activity, and conduct a longer-term follow up of intervention effects.

One of the key strengths of the current study is the theoretical basis and the provision to test the mechanisms of effectiveness of the intervention. The current intervention is based on the trans-contextual model [10], which provides a clear basis for the mechanisms of the proposed intervention effects. Specifically, we expect the autonomy-supportive intervention delivered by PE teachers to lead to changes in students’ autonomous motivation in school and outside of school, and their beliefs and intentions toward physical activity outside of school. We will test the effects of the proposed intervention on these theory-based constructs as secondary outcomes in the current intervention. Furthermore, because we plan to collect long-term follow up data we will be able to ascertain whether changes in the psychological constructs as a result of the intervention are maintained over time. The current study is the first to specifically design an intervention using this model and to test the theory-based mechanisms of intervention effects.

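### At one, three and six months the plan adjusts for the previous, post-randomisation occasion, which attenuates a maintained intervention effect and conflicts with the stated pre-trial reference

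*Protocol article*

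**What the plan says.** The Data analysis section fixes one model for the intervention effect: "We will test the model at each of the follow-up time points with students’ out-of-school physical activity as the primary dependent variable". Its predictors are a condition dummy and, simultaneously, the psychological constructs of the trans-contextual model. The adjustment rule follows: "We will statistically control for each of model variables from the previous time point using the standardized residual scores". Physical activity is one of the model variables, and it is measured "at the pre-trial, post-trial, one-, three and 6 month follow-up data collection occasions" (Primary outcome variable).

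The aims are worded differently. The Objectives evaluate effects through changes in students' "physical activity levels and trans-contextual model variables relative to pre-trial baseline measures". Of the trial's contribution, the Discussion says that "it will evaluate the long-term effectiveness of the intervention in promoting physical activity behaviour through one, three, and six-month post-intervention follow-up". It also wants to learn whether "changes in the psychological constructs as a result of the intervention are maintained over time".

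No section says that the later models use pre-trial values instead, or that effects are accumulated over occasions. The Sample size section describes the same regression without any previous-occasion adjustment. The remark in Data analysis about examining trajectories names no model and no treatment contrast.

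**The concern.** Adjusting for a value measured before allocation is sound, because the arms differ there only by chance. Adjusting for a value measured after the intervention is a different matter, because part of the effect sits inside the covariate and is subtracted with it. Three of the four follow-up tests of the primary outcome are of this second kind.

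What is at stake is the reading of persistence. A benefit that held steady from post-trial onwards would show as a clearly smaller coefficient at the next occasion, and could be reported as fading. A benefit that faded in part could be reported as absent, or as slight harm. These are the questions that the later follow-ups were added to answer.

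**Working it through.** **Which occasion is the covariate?** From the list of occasions under Primary outcome variable:

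| Tested at | Previous occasion | Measured before the intervention? |
|---|---|---|
| Post-trial | Pre-trial | Yes |
| One month | Post-trial | No |
| Three months | One month | No |
| Six months | Three months | No |

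**Formula.** Let d(t) be the true difference between arms at occasion t in SD units, with equal SDs and within-arm correlation r between adjacent occasions. The within-arm slope of the outcome on the previous occasion is r, so the adjusted difference is

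d(t) − r × d(t−1).

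At pre-trial, randomisation makes the expected difference 0, so adjusting for pre-trial estimates d(t). If the effect is constant at d, adjusting for the previous occasion estimates d − r × d = d × (1 − r).

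**Inputs.** The article gives neither r nor an effect size. Both are assumed here: r from 0.3 to 0.8 and d = 0.30 SD. For power, 286 / 2 = 143 students per arm comes from the analysed sample in the Sample size section. A two-sided 5% level is assumed (the article gives 0.05 without sidedness), and clustering by school and class is ignored.

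**Maintained effect at one and three months.** The last column takes an effect that would have 90% power under pre-trial adjustment. Its power under previous-occasion adjustment, with the same residual SD, is Φ(3.24 × (1 − r) − 1.96), where 3.24 = 1.96 + 1.28.

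| r | Share retained, 1 − r | 0.30 × (1 − r) | Power in place of 90% |
|---|---|---|---|
| 0.3 | 70% | 0.21 | 62% |
| 0.4 | 60% | 0.18 | 49% |
| 0.5 | 50% | 0.15 | 37% |
| 0.6 | 40% | 0.12 | 25% |
| 0.7 | 30% | 0.09 | 16% |
| 0.8 | 20% | 0.06 | 9.5% |

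The power figures show relative loss only. With clustering the absolute values would differ.

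**Simulation check.** With 200,000 students, a constant 0.30 effect and r = 0.6, previous-occasion adjustment gave 0.118, 0.120 and 0.116 at the three later occasions under equal correlations, and 0.121, 0.119 and 0.118 under first-order autoregressive correlations. The formula gives 0.120. Pre-trial adjustment gave 0.296 to 0.300 in the same runs. Forming residual scores in a separate step gave nearly the same answer (0.114 to 0.118), so the attenuation does not depend on how the control is carried out.

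**Partly maintained effect.** Take 0.30 at post-trial and r = 0.5. A true one-month effect of 0.15 gives 0.15 − 0.5 × 0.30 = 0. A true one-month effect of 0.10 gives 0.10 − 0.15 = −0.05, a real remaining benefit with the wrong sign.

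**What the calculation leaves out.** It contains only arm and one earlier value of the outcome. The planned model also enters the concurrent mediators, and at six months the controls have been trained. It isolates the effect of the lag rule and does not predict the trial's estimates.

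**The case against.** The strongest reply has four parts.

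1. Previous-occasion control is a recognised specification for a process model, and the trial does want to test mechanisms. This stands, and lagged adjustment is not wrong in itself. The difficulty is that the article names no other model from which to read the intervention effect.

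2. The wording may be loose drafting in a condensed article, with pre-trial intended throughout. That is possible. The sentence is nevertheless a positive statement of a rule and not an omission, and for three of the four follow-ups it says something other than the Objectives do. It needs correcting either way.

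3. Replacing the covariate would not by itself recover the full effect. This is right. A reader might infer from the simulation that pre-trial adjustment would return the whole 0.30 SD in this trial. The article does not support that. The same model conditions on the intended mediators, so its condition coefficient is a direct effect at every occasion, post-trial included. In addition, under Procedure and data collection methods, the control group receives the training immediately after the three-month occasion, so a constant difference at six months is not a safe premise.

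4. The residual scores put the effect in SD units. A reader might take this as a second error. It is mainly a matter of presentation, and the check above shows no separate harm, so it is not part of this point.

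**Conclusion.** The rule is wrong as written for the one-, three- and six-month tests. It conflicts with the pre-trial reference in the Objectives and with the long-term and maintenance aims in the Discussion. The lag rule does no damage at post-trial.

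The size is (1 − r) of a fully maintained effect: 60% retained at r = 0.4, 50% at 0.5, 30% at 0.7. This rests on equal SDs, an assumed r, a constant effect and no allowance for clustering. The direction of the distortion for a maintained effect follows for any positive r, but the percentage cannot be fixed from the article.

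A reader might infer that the coefficient captures only new change since the last visit, so that a maintained effect vanishes. That goes too far: the effect is reduced in proportion to r and disappears only as r approaches 1. At six months the contrast is with controls who have since been trained, so the table should not be applied there without that qualification.

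**What to change.** State two models in Data analysis.

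- **Total effect.** At every follow-up, estimate the intervention effect with adjustment for the pre-trial value of the outcome and pre-trial covariates. Condition on no post-randomisation value, whether an earlier follow-up or a concurrent mediator. A single longitudinal model with pre-trial as covariate and a treatment contrast at each occasion would also serve.
- **Process model (secondary).** Keep the previous-occasion control and the simultaneous psychological predictors here, for mediation or cross-lagged questions, and say that the intervention effect will not be read from it.

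Add that the six-month contrast will be interpreted separately, because pre-trial adjustment does not restore an untreated comparison once the control group has been trained.

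The cost is a short rewrite of the analysis paragraph and one additional model per occasion. The pre-trial measurements are already scheduled, so no new data are needed. Changing the covariate sentence alone would not be enough, because the mediators would still be conditioned on.
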